6.2.7 Viral Load

HIV-1 RNA must be performed at screening and at subsequent study visits by a laboratory that possesses a CLIA certification or equivalent. The laboratory also must be certified by the DAIDS Virology Quality Assurance (VQA) Program or its Canadian equivalent, as the viral load determination is a primary endpoint of the study.

6.2.8 HIV EIA/WB (ELISA and Western Blot)

This will include the results of HIV antibody ELISA testing as well as Western Blot test results (done using approved assays in certified laboratories). If the Western Blot test result is not positive at the time of initial evaluation, it will be repeated at each study visit until the criteria for a positive test result are met. If the ELISA and Western Blot test results are positive at the time of initial evaluation and the diagnosis of acute/early HIV infection is in doubt, an aliquot of the initial sample will be shipped to a central laboratory for the performance of a detuned antibody ELISA assay.

6.2.9 Repository

At screening and again at months 1, 3,4,6,8,10,12 and then quarterly, expanded phlebotomy for the storage of plasma and cells will be performed. A minimum of 15 mL and a maximum of 50 mL will be collected for this purpose, to permit future studies on pertinent hypotheses of the pathophysiology of acute/early HIV infection. At other visits after month 1, 10 mL will be collected. Serum and plasma will be stored at -80^o^C in aliquots of 0.5 mL. Mononuclear cells will be cryopreserved using controlled-rate freezing and stored at -135^o^C in aliquots of 5-10 x 10^6^ cells/vial.

6.2.10 Genotype

At selected time points, a plasma sample will be taken for the performance of genotypic drug resistance testing in local laboratories. Samples that cannot be processed in this manner will be sent to the academic laboratory of [name] at the University of British Columbia, where they will be analyzed using the TruGene Assay (Bayer Diagnostics, Mississauga, ON, Canada).

### 6.3 Off-Drug Requirements

### Additional safety monitoring and reporting of serious adverse experiences (SAEs) continue to be required upon completion or discontinuation of study treatment regardless of whether a protocol follow-up period is scheduled to occur. As specified in the current Division of AIDS *Serious Adverse Experience (SAE) Reporting Manual,* adverse experiences occurring during the immediate 8-week period after the last dose of study treatment which meet SAE reporting requirements must be reported to the DAIDS according to the SAE reporting procedures listed in section 11.4.

## 7.0 TOXICITY MANAGEMENT

##

For patients randomized to receive treatment, the HAART regimen will be selected or adjusted based on the results of the genotypic resistance test done at the time of screening. Selection and/or adjustment will be done by the study physician, who will then inform the chair or co-chair (in the case when neither the chair nor the co-chair is the treating physician) of the choice. The standard ACTG/CTN approach will be used to grade and address drug toxicity on an ongoing basis. There will be no protocol-mandated criteria for a substitution or discontinuation of HAART, such decisions being left to the standards of clinical practice, with all drug-associated toxicities being documented. Drug substitutions within the same class of drug (NRTI for NRTI, NNRTI for NNRTI or PI for PI) will be preferred, as decided by the study physician, but changes across classes will also be permitted. If the chair or co-chair of the protocol is not the treating physician, they will be informed of all decisions to change or discontinue HAART regimens on the monthly conference calls.

## 8.0 CRITERIA FOR TREATMENT DISCONTINUATION

- Drug-related toxicity (see section 7.0 Toxicity Management).
- Development of medical condition which makes it necessary to temporarily or permanently discontinue medication in the opinion of the study investigator.
- Requirement for prohibited concomitant medications (see section 5.4)
- Failure by the subject to attend three consecutive monthly visits.
- Subject repeatedly noncompliant with study medications as prescribed.
- Request by the subject to withdraw.
- Request of the primary care provider if s/he thinks the study is no longer in the best interest of the subject.
- Clinical reasons believed life threatening by the study physician, even if not addressed in the toxicity management of the protocol.
- Subject judged by the investigator to be at significant risk of failing to comply with the provisions of the protocol as to cause harm to self or seriously interfere with the validity of study results.
- Subject reaches a defined study endpoint, if applicable.
- At the discretion of the NIAID, CTN, investigator, or other regulatory authority.

## 9.0 STATISTICAL CONSIDERATIONS

Any patient who is randomized will be evaluated. Parametric and distribution-free statistical methods will be used to analyze quantitative and qualitative/categorical data. Within group comparisons of baseline and follow-up measurements of plasma viral load (log-transformed) and CD4 lymphocyte counts will be conducted using Student’s paired t-test. For the principal study endpoint, a comparison of the mean log-transformed plasma viral load measures 24 months after the initial presentation in all treated vs. untreated subjects will be carried out using Student’s unpaired t-test and repeated measures analysis of variance. A similar approach will be taken to the comparison of plasma viral load measures at other time points or between sub-groups. Absolute CD4 lymphocyte counts will be treated in the same way. For issues of immunologic disease progression (defined as CD4 cell count < 350 cells/mm^3,^, and requiring a consideration of HAART), survival analytic methods (e.g. Kaplan-Meier, Cox proportional hazard regression) will be used. For other data (such as drug toxicity and treatment discontinuation), descriptive statistics will be used, with appropriate comparisons between groups as indicated.

### 9.1 General Design Issues

###

### 9.2 Endpoints

9.2.1 Primary Endpoints

- Comparison of the plasma viral load 24 months after initial presentation in all treated vs. untreated patients.

9.2.2 Secondary Endpoints

- Comparison of the plasma viral load 36 months after initial presentation in all treated vs. untreated patients.
- Comparison of the CD4 lymphocyte count 24 and 36 months after initial presentation in all treated vs. untreated patients.
- Comparison of the plasma viral load 24 and 36 months after initial presentation in patients treated in the acute vs. early stage of infection.
- Comparison of the CD4 lymphocyte count 24 and 36 months after initial presentation in patients treated in the acute vs. early stage of infection.
- Toxicity of HAART in all treated patients.

### 9.3 Randomization and Stratification

### 9.4 Sample Size and Accrual

###

Viral load set points will be evaluated at 12 and 24 months after completion of the 12 months randomization period, i.e., 24 and 36 months after entry into the study. For each patient, we observe the viral load at the pre-defined times and compare the treated and untreated groups. Based on preliminary studies at Weill Cornell School of Medicine in which the mean viral load set point after stopping HAART was 4.2 log_10_ copies/ml with SD = 0.5 log_10_ copies/mL, we anticipate a standard deviation of 0.5 log_10_ copies/mL for the plasma viral load at the times this endpoint will be measured. This is illustrated in the sample size tables below. Further, based on data from the study by Mellors et al from the MACS, which suggest that a difference of 0.25 log_10_ copies/mL may confer a meaningful long-term clinical benefit, we have evaluated our expected power to detect a difference of this magnitude. Based on these assumptions, we can calculate the number of patients/group that would be required to achieve a given power for detecting a specific measured virologic benefit of TL-HAART:

| Virologic Benefit of TL-HAART | N/group for β=0.80 | N/group for β=0.90 |
| --- | --- | --- |
| 0.25 log_10_ copies/mL | 64 (93, 144)^*^ | 84 (121,189) |
| 0.50 log_10_ copies/mL | 16 (24,36) | 21 (31,48) |
| 0.75 log_10_ copies/mL | 7 (11,16) | 10 (14,21) |

* Power assuming a standard deviation of 0.5 (0.6, 0.75) log_10_ copies/ml of HIV RNA, and α=0.05.

Thus, with our projected enrollment of 180 subjects, we would have 90 subjects per group which would give us more than 90% power to detect a benefit as small as 0.25 log_10_ copies/mL. If the difference is only slightly greater, we will be able to detect it with β > 0.95. If need be, the sample size could be increased by extending the recruitment period to 30 months rather than 24. If we more conservatively estimate that the standard deviation of the observations of viral load set points will be somewhat larger, e.g., 0.6 or 0.75 log_10_ copies/mL of HIV RNA (as observed by Gallant et al (27) over a longer time period with a more heterogeneous group than we will study), rather than 0.5, then the sample size may still be large enough to detect a difference of 0.25 log_10_ copies/ml of HIV RNA with a power of 0.8. Some would argue that the greatest (and most significant) differences will be present in subjects infected most recently (acute) . It is our intention to recruit 60 such subjects (30/group) in addition to the 120 patients enrolled in the early stage of infection. With this recruitment, the following table shows the power of the study as a function of the expected virologic benefit:

| Virologic Benefits of TL-HAART | Infected 0-2 mo (30/group) | Infected 2-12 mo (60/group) | Infected 0-12 mo (60/group) |
| --- | --- | --- | --- |
| 0.25 log_10_ copies/mL | 35% (26,18)* | 61% (46,32) | 78% (63,45) |
| 0.50 log_10_ copies/mL | 89% (75,56) | 99% (96,85) | > 99% (99,95) |
| 0.75 log_10_ copies/mL | > 99% (98,89) | > 99% (>99,99) | > 99% (>99,99) |

* Power assuming a standard deviation of 0.5 (0.6, 0. 75) log_10_ copies/ml of HIV RNA, and α=0.05.

If the standard deviation of the viral load set points is 0.5 log_10_ copies/mL, the study is more than adequately powered to detect a difference of 0.25 log_10_ copies/mL unless only a relatively small benefit of treatment is observed only in the acute sub-group. . If the standard deviation is larger, the ability to find a difference of 0.25 log_10_ copies/mL is reduced for this sub-group, but remains high for larger treatment effects. If there is substantial variation in disease progression across individuals, the power will be lower than that given in the table and larger sample sizes would be needed. This is because the variability of the changes includes not only the measurement error associated with the viral load assay but also natural variation in disease progression across individuals (irrespective of whether they are on or off treatment) and/or a differential effect of treatment across individuals. If this were true, the assumed standard deviation of plasma viral load of 0.5 log_10_ copies/mL would be an underestimate. However, it is extremely unlikely that this situation pertains. The standard deviations on which we have based our calculations were observed in real studies in which HAART was discontinued and patients were followed. Therefore, they take into account at least some of the variability in disease course that may pertain to the situation of our study. For this reason, we are quite confident that the protocol we have put forward is feasible and will address the issue for which it is designed.

**Patient Recruitment** - All patients in whom a diagnosis of AIED can be made will be offered the opportunity to participate in the study. Over two years, we will recruit 180 patients into the protocol, including significant numbers of IDUs, including 48 in Baltimore and 132 at Canadian sites (overall, 1-2/week in all the sites combined).

**Recruitment at Canadian sites -** In order to enhance recruitment, we have developed centralized clinical infrastructures in Vancouver. This serves to facilitate outreach efforts for subject enrolment with an emphasis on IDUs and women who do not easily access health care (including Aboriginal women), provide community-based nursing and laboratory support for health care centers and community clinics that wish to enroll subjects and co-ordinate their follow up. *Providence Health Care:* This is the tertiary care hospital center at which all of the participating Vancouver physicians have admitting privileges. It houses a dedicated 18-bed HIV ward. The emergency room is the preferred point of initial contact for IDUs in the vicinity, who may not yet be known to be infected with HIV. It is accepted practice to perform HIV testing on these individuals on a routine basis. **In the past 4 years, a mean of 8 patients/year has been referred to our AIED program**. *Community Physicians/AIDS Service Organizations:* They have been targeted by presentations on AIED at local meetings, and distribution of a postcard in prominent community locations. This system is **expected to continue to yield a mean of 16 patients/year**. *Provincial Reference Laboratory:* This laboratory, located in Vancouver, performs all HIV antibody testing for the province of British Columbia. There are 450 new positive tests every year. About 30-40 patients/year test positive and do not have a family physician and may be referred into our study. **We expect 6 referrals/year**. *Vancouver Coastal Health Authority:* [name] is the Consultant in Infectious Diseases Specialist based at the Pender Community Health Center, which provides care for 200 HIV-infected individuals, including 6 new referrals/month. This clinic, which caters mostly to IDUs, is also linked to three other clinics in the area, collectively providing care to another 200 HIV-infected individuals, including 3-5 new referrals/month: a) Three Pillars Clinic ([name]); b) Portland Hotel Clinic ([name]); and c) Yaletown Clinic ([name]). **This network is expected to yield 12 AIED patients/year**. We will keep in contact with private physicians who have large HIV patient bases and who regularly refer patients to us at regular intervals. We will also provide feedback to each physician source. **This is expected to yield 8 patients/year**. After major conferences, [name] is often the invited speaker at HIV Update dinner meetings which are very well attended by the local HIV medical community. This will represent a unique opportunity to publicize findings in the field of AIED and enhance the study’s visibility. This is **expected to yield 6 patients/year**. **Our projection of 50 new AIED patients/year in Vancouver is entirely realistic**. *Cool Aid Community Health Centre, Victoria:* This is a community and referral clinic in downtown Victoria (active census 200 patients), directed by [name], a HIV/addiction specialist. **It is expected to generate 8 referrals/year**. *Sunnybrook Hospital HIV Clinic, Toronto:* This is a tertiary care HIV referral clinic in Toronto, under the direction of [name]. **It is expected to generate 10 new referrals/year**. *Clinique Médicale du Quartier Latin, Montreal:* This is a large HIV clinic in Montreal, with over 2,000 patients. [name] is its research director, and the clinic has a total of three full time research coordinators in addition to outreach workers. Over the past two years, it has been active within the Canadian portion of the AIEDRP network and has enrolled 37 patients (30 men, 7 women). **We project a continued enrollment of 12 patients/year.**

**Recruitment in Baltimore -** *ALIVE I/II Cohort Study*. These are NIDA-funded cohort studies of the natural history of HIV infection in IDUs (ALIVE I) and risk factors for infection with HIV among seronegative IDUs (ALIVE II). This population is almost entirely African American. All HIV negative participants in these studies are screened every 6 months for HIV infection. ALIVE II ([name]), principal investigator) has received funding through 2008. *The Johns Hopkins Hospital HIV Service*. The Moore clinic follows 3100 HIV infected people, mostly African American (78%) and male (67%). *Chase-Brexton Health Services (CBHS) -* This large multi-disciplinary clinic is located in mid-town Baltimore city and provides HIV and other primary care services to over 1,100 patients; *Baltimore City Health Department Sexually Transmitted Disease (STD) Clinics* - The Johns Hopkins Infectious Diseases Division provides professional staff for the clinical operation of the STD clinics. Approximately 30,000 patient-visits occur annually in two city STD clinics in which the HIV seroprevalence is 5.2%. Other sources will include *Local Hospital inpatient wards; Community Physicians and Clinics;* *Clinic Based Recruitment.* We will also provide feedback to each physician source. After major HIV Conferences and Dinner meetings outside of Baltimore, there are several HIV Update dinner meetings, which are very well attended by the local HIV medical community. **Based on the track record of these sources, we anticipate enrolling 24 patients/year into the study.**

**Strategies for Retention –** In keeping with current practices, we will pay $15 (Baltimore) or $8 (Canada) per study visit. Participants will receive an appointment card at each visit, which includes telephone numbers and pager numbers of study staff. Locator forms will be obtained at baseline and updated every 3 months. Attempts to reschedule missed visits are made immediately with subsequent follow-up by a social worker, pharmacist or other relevant health care professional. We will also search hospital and correctional institution databases for recent admissions. We would also consider off-site visits (e.g. to participant’s homes, outside clinics). The study staff is devoted to services that will encourage continued participation by the participant providing flexibility in scheduling (e.g., evening visits), providing basic counseling and referral services as required, coordinating appointments and blood draws with their medical providers, and being available to discuss the many concerns that surface upon receiving a new HIV diagnosis. Referrals for professional counseling and support are provided as needed, and review of laboratory results and their significance occurs at each visit.

###

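### Section 9.4 suggests 80% power for 0.25 log10 even at SD 0.75, but its own table needs 144 per group; 90 per group gives about 60%

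*Protocol*

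**What the plan says.** Protocol 9.4 sets the target difference from a cohort finding that "a difference of 0.25 log_10_ copies/mL may confer a meaningful long-term clinical benefit". For the spread, "we anticipate a standard deviation of 0.5 log_10_ copies/mL for the plasma viral load", taken from preliminary data in patients who had stopped HAART.

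The first table gives the number per group for a 0.25 log10 difference as 64 (93, 144) for 80% power and 84 (121, 189) for 90% power. Its footnote reads: "Power assuming a standard deviation of 0.5 (0.6, 0.75) log_10_ copies/ml of HIV RNA, and α=0.05".

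The text then says "we would have 90 subjects per group which would give us more than 90% power" for that difference. It goes on to consider a larger spread, "e.g., 0.6 or 0.75 log_10_ copies/mL of HIV RNA", which it attributes to a longer observation period in a more heterogeneous group, and says that in this case "then the sample size may still be large enough to detect a difference of 0.25" log10 with power 0.8.

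The second table gives power for 0.25 log10 by stage of infection. Its all-patient column is headed 60 per group and reads 78% (63, 45). The following paragraph grants that wide variation between individuals would lower power, and then says "it is extremely unlikely that this situation pertains".

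Section 9.4 gives no rate of loss to follow-up. Section 9.6 expects some withdrawals before month 24 and estimates the missing values by regression.

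**The concern.** The statement about a larger SD can be checked against the table printed just before it. At SD 0.75 that table asks for 54 more patients per group than the trial will have. A sponsor, ethics committee or monitoring board that reads the prose rather than the table would believe the trial is adequately powered for its chosen difference across the whole SD range considered. If the SD turned out near 0.75, a non-significant result could then be read as evidence against a 0.25 log10 benefit, when the trial had roughly a two-in-five chance of missing one.

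A smaller point sits beside it. The figure above 90% at SD 0.5 counts every randomised patient as evaluable at month 24, and the margin over the required number is thin.

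**Working it through.** **Inputs (all from 9.4).** Difference 0.25 log10; SD 0.5, 0.6 or 0.75; α 0.05; 90 per group. Sidedness is not stated. I take two-sided, because that reproduces the table and one-sided does not (one-sided gives 50, 72 and 112 for 80% power).

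**Step 1: reproduce the first table.** n per group = 2(z₀.₉₇₅ + z_power)² × (SD/0.25)².

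- 80% power: 2 × (1.960 + 0.842)² = 15.70. Multiplied by 4, 5.76 and 9, this gives 62.8, 90.4 and 141.3. The t-test gives 64, 92 and 143. Printed: 64, 93, 144.
- 90% power: 2 × (1.960 + 1.282)² = 21.0. This gives 84.1, 121.0 and 189.1. The t-test gives 86, 123 and 191. Printed: 84, 121, 189.

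The table is sound.

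**Step 2: power with 90 per group.** Power = Φ(0.25/(SD × √(2/90)) − 1.96), with √(2/90) = 0.1491.

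| SD | 0.25/(SD × 0.1491) | Power, normal | Power, t-test | Table's n for 80% |
|---|---|---|---|---|
| 0.5 | 3.354 | 91.8% | 91.6% | 64 |
| 0.6 | 2.795 | 79.8% | 79.4% | 93 |
| 0.75 | 2.236 | 60.9% | 60.4% | 144 |

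The largest SD that gives 80% power with 90 per group is about 0.60. Even a one-sided test reaches only 72% at SD 0.75.

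**Step 3: the recruitment extension.** Assuming constant accrual, 180 × 30/24 = 225, or about 112 per group. T-test power is then 96%, 87% and 70% at SD 0.5, 0.6 and 0.75.

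**Step 4: loss to follow-up.** The surplus over the table's requirement for 90% power is 90 − 84 = 6, or 6/90 = 6.7%. Over the t-test requirement it is 90 − 86 = 4, or 4.4%. T-test power under assumed loss rates (the documents give none):

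| Loss | Evaluable per group | SD 0.5 | SD 0.6 | SD 0.75 |
|---|---|---|---|---|
| 0% | 90 | 91.6% | 79.4% | 60.4% |
| 5% | 85.5 | 90.2% | 77.3% | 58.2% |
| 10% | 81 | 88.5% | 75.0% | 55.9% |
| 20% | 72 | 84.6% | 70.0% | 51.1% |

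At SD 0.5, power stays at 80% or more until loss reaches about 29%.

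**Step 5: the second table, 0.25 log10 row.** T-test power at SD 0.5 (0.6, 0.75):

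| Column | Printed | At the planned n | At the n that fits |
|---|---|---|---|
| Acute | 35 (26, 18) | 30: 48 (36, 25) | 20: 34 (25, 18) |
| Early | 61 (46, 32) | 60: 78 (62, 44) | 40: 60 (45, 31) |
| All | 78 (63, 45) | 90: 92 (79, 60) | 60: 78 (62, 44) |

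The row appears to describe a trial of 120, not 180. The all-patient column is headed 60 per group although 30 + 60 = 90. On either reading, power at SD 0.75 is far below 80%.

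**The case against.** The protocol's wording is hedged (may still), the adverse sample sizes are printed nearby, and at SD 0.6 the hedge is fair: 79% is 80% for practical purposes, and the extension would bring it to 87%. That stands. The hedge does not stretch to 0.75, where the section's own table settles the matter and the extension does not close the gap.

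The primary analysis in 9.6 adjusts for baseline viral load and CD4 count, which can shrink the residual SD to SD × √(1 − r²). This also stands in principle, but no correlation r is given. At SD 0.75 with 90 per group, assumed values of r of 0.3, 0.5 and 0.6 give 65%, 73% and 79%, so r would have to exceed about 0.6 to rescue the claim. The tables in 9.4 use the unadjusted SD.

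Two stronger readings are tempting. A reader might infer that the figure above 90% is wrong, or that the protocol promises its power will survive dropout. Neither is supported: the figure is right for 90 evaluable per group, and 9.4 says nothing about dropout. The 10% and 20% rates above are illustrations. A reader might also infer that 0.75 is the SD to expect. The protocol attributes the larger values to a longer period and a more mixed population, and its judgement that wide variation is unlikely cannot be tested from the document.

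**Conclusion.** The point holds in a limited form. With 90 per group the suggestion of 80% power for 0.25 log10 is about right at SD 0.6 (79%) and wrong at SD 0.75 (60%, or about 70% with a 30-month recruitment at constant accrual). The power above 90% at SD 0.5 is correct at about 92%, but falls below 90% once loss exceeds roughly 5 to 7%; the lower end uses the t-test requirement and the upper end the protocol's table. The second table does not match the planned group sizes and needs correcting along with the sentence.

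These figures assume a two-sided 0.05 test, equal allocation and no baseline adjustment. The error lies in the stated power. It does not show that the trial is underpowered at the SD it anticipates.

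**What to change.** 1. Replace the sentence on larger SDs with: for 0.25 log10 (unadjusted, two-sided 0.05, 90 evaluable per group), power is about 92%, 79% and 60% at SD 0.5, 0.6 and 0.75.
2. Add, labelled as an illustration because no loss rate is planned: if 10% lack month-24 data, about 88%, 75% and 56%.
3. Note that the baseline adjustment in 9.6 may raise these figures by an amount that cannot be stated without a baseline-outcome correlation.
4. Recompute the second table for 30, 60 and 90 per group and correct the heading of the last column. The 0.25 row becomes 48% (36, 25), 78% (62, 44) and 92% (79, 60). The 0.50 row becomes 97% (89, 72), >99% (>99, 95) and >99% (>99, >99).
5. In the paragraph after that table, limit the assurance of adequate whole-trial power for 0.25 log10 to an SD of about 0.6 or less. At present it describes the loss of power at larger SDs as affecting the acute sub-group only.

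The cost is text only. No design change follows, and the stated power becomes less favourable at the larger SDs. I do not suggest tying the recruitment extension to an observed SD: with 24 months of recruitment and a month-24 endpoint, few patients would have endpoint values when that decision fell due.

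### Section 9.4 says power of 0.8 for 0.25 log10 may survive an SD of 0.6 or 0.75; this is essentially true at 0.6 but false at 0.75, where 90 per group gives about 60%

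*Protocol*

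**What the plan says.** All of this is in Protocol section 9.4.

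- **Target difference:** "a difference of 0.25 log_10_ copies/mL may confer a meaningful long-term clinical benefit".
- **Planning SD:** "we anticipate a standard deviation of 0.5 log_10_ copies/mL for the plasma viral load".
- **First table:** for a power of 0.80 to detect 0.25 log10, it prints 64 per group, with 93 and 144 in brackets. The footnote explains the three entries: "Power assuming a standard deviation of 0.5 (0.6, 0.75) log_10_ copies/ml of HIV RNA, and α=0.05".
- **Planned size:** "with our projected enrollment of 180 subjects, we would have 90 subjects per group".
- **Contingency:** if needed, "the sample size could be increased by extending the recruitment period to 30 months rather than 24". No resulting number of patients is given.
- **Statement at issue:** if the SD "will be somewhat larger, e.g., 0.6 or 0.75 log_10_ copies/mL of HIV RNA", "the sample size may still be large enough to detect a difference of 0.25" log10, at a power of 0.8.
- **Second table:** the whole-study column (infected 0-12 months) prints 78% (63, 45) for 0.25 log10 at the same three SDs. It is headed 60 per group.

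**The concern.** The first table and the later sentence use the same difference, the same SDs and the same target power, and they disagree at SD 0.75. With 90 per group the trial is 3 per group short of the table at SD 0.6, but 54 per group short at SD 0.75 (180 of the 288 patients required).

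The larger SDs are the protocol's own conservative case, which it attributes to a cited treatment-interruption study in a more heterogeneous group. A sponsor or DSMB member who relies on the sentence would think that 80% power may survive at SD 0.75, when the chance of missing a true 0.25 log10 benefit would be about 40%. That bears on whether an extension is worth making and on how a null result is read.

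**Working it through.** **Inputs (all from section 9.4).** Difference 0.25 log10; SD 0.5, 0.6 or 0.75; alpha 0.05; 90 per group. Sidedness is not stated and is settled in step 1.

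**1. Reproduce the first table.** Normal approximation, two-sided: n per group = 2 × (1.960 + 0.842)² × (SD/0.25)² = 15.70 × (SD/0.25)².

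| SD | (SD/0.25)² | n, normal | n, t-test | Printed |
|---|---|---|---|---|
| 0.5 | 4.00 | 63 | 64 | 64 |
| 0.6 | 5.76 | 91 | 92 | 93 |
| 0.75 | 9.00 | 142 | 143 | 144 |

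One-sided, the numbers would be 50, 72 and 112, which do not match. The table is therefore two-sided and sound.

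**2. Power with 90 per group.** Power = Φ(0.25 / (SD × √(2/90)) − 1.960), where √(2/90) = 0.1491.

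- SD 0.5: Φ(3.354 − 1.960) = 91.8% (t-test 91.6%). This matches the protocol's claim of more than 90%.
- SD 0.6: Φ(2.795 − 1.960) = 79.8% (t-test 79.4%).
- SD 0.75: Φ(2.236 − 1.960) = 60.9% (t-test 60.4%).

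The largest SD that keeps 80% power with 90 per group is about 0.595. At SD 0.75 the difference detectable with 80% power is 0.25 × 0.75/0.595 = 0.315, about 0.31 log10.

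**3. The 30-month extension.** The protocol gives no number, so two accrual assumptions are used.

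- Planned rate held constant: 180/24 = 7.5 per month, so 30 months gives 225 patients (112.5 per group).
- Upper case, with every projected patient or referral in the site recruitment paragraphs randomized: 50 + 8 + 10 + 12 + 24 = 104 per year, × 2.5 = 260 patients (130 per group).

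| Total N | Power at SD 0.6 (t-test) | Power at SD 0.75 (t-test) |
|---|---|---|
| 180 | 79.4% | 60.4% |
| 225 | 87.5% | 70.2% |
| 260 | 91.7% | 76.3% |
| 288 | 94.1% | 80.5% |

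Reaching 288 at 7.5 per month would take 288/7.5 = 38.4 months.

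**4. The second table.** At 60 per group the normal approximation gives 78.2%, 62.6% and 44.7% for 0.25 log10, which is the printed 78% (63, 45). The whole-study column was therefore computed for 60 per group, although the two subgroups are planned at 30 + 60 = 90 per group. It does not describe the planned trial.

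**The case against.** **The sentence is hedged, and one of its two examples is right.** This stands for SD 0.6: a shortfall of 3 per group is trivial. A reader might infer from the table that the sentence is wrong at both SDs, and the figures do not support that. The hedge does not help at 0.75, because once SD, difference, alpha and sample size are fixed, power is determined.

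**The protocol says more about larger SDs elsewhere in 9.4.** This also stands. A reader might take the sentence as the plan's only statement on a failed variance assumption. It is not: the first table gives sample sizes at both larger SDs, the second prints 63% and 45% for the whole study, and the text after it allows that substantial variation between individuals would lower power. None of this corrects the 0.8 figure. The second table is for 60 per group. The following text ties the loss at larger SDs to the acute subgroup, and it calls the case of substantial individual variation extremely unlikely.

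**The extension is not claimed to rescue SD 0.75.** Correct: it is offered before the larger SDs are discussed, and it would secure SD 0.6. To call it useless would be too strong. Equally, reading the statement as referring to the extended sample does not save it at 0.75.

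**The analysis in section 9.6 adjusts for baseline viral load and CD4 count, which can raise power.** True in principle. With an assumed outcome-baseline correlation r, the residual SD is 0.75 × √(1 − r²). With 90 per group, r = 0.4 gives 68% and r = 0.6 gives 79%. Reaching 80% needs r of about 0.46 with 225 patients and about 0.3 with 260. The protocol states no correlation and its tables use none, so adjustment cannot support the printed 0.8, but any replacement figure should be labelled unadjusted. Missing data pull the other way: an assumed 10-20% loss lowers power at SD 0.75 to about 56-51%.

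**A null result is read from its confidence interval.** Fair, and it limits the harm.

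**Conclusion.** The statement holds at SD 0.6 (about 79%) and fails at SD 0.75, where the protocol's own table needs 144 per group and 90 per group gives about 60%. A 30-month recruitment period brings SD 0.6 to about 87% or more, but leaves SD 0.75 at about 70% (225 patients) to 76% (260 patients).

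The power figures rest on an unadjusted two-sided t-test at alpha 0.05, equal groups and no loss to follow-up. The extension figures also rest on the accrual assumptions shown. A reader might go further and infer that the planning SD of 0.5 is wrong or that the trial is too small. This point supports neither: at SD 0.5 the claim of more than 90% power reproduces. The error is one overextended example in the sensitivity statement, worth correcting because it contradicts the table above it and costs little to put right.

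**What to change.** In section 9.4:

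1. Limit the statement about a power of 0.8 to SD 0.6 (about 79% with 90 per group).
2. Add that at SD 0.75 the power for 0.25 log10 with 90 per group is about 60%, and that the difference detectable with 80% power is about 0.31 log10.
3. Beside the extension to 30 months, state that power at SD 0.75 would be about 70% with 225 patients (7.5 per month) and about 76% with 260 (all site projections met), and name these as accrual assumptions.
4. Label all these figures as unadjusted for baseline and before any loss to follow-up.
5. Reconcile the whole-study column of the second table with the planned 90 per group. Otherwise the corrected text would sit directly above 63% and 45% at the same SDs.

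The cost is wording and a recomputed table column. One stated power becomes less favourable at SD 0.75. Sample size, endpoint, analysis and conduct are unchanged, and no extra patients are requested.
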